### Randomization and blinding

2.5

Participants will be randomly assigned (2:1) to receive intravenous dexamethasone or placebo. The National Health and Medical Research Council Clinical Trials Centre, Sydney, Australia provides the randomization setup via their automated telephone-based interactive voice response services. Randomization is minimized for:

(i)A score of <2 versus ≥2 using the predictive score of Chalmers et al^[6]^ for the development of complicated pleural effusion/empyema secondary to pneumonia (one point each for: serum albumin <30 g/L, CRP >100 mg/L, platelet count >400 × 10^9^/L, serum sodium <130 mmol/L, intravenous drug use, and chronic alcohol excess. One point will be deducted for the presence of COPD);(ii)Known history of diabetes mellitus (vs not); and(iii)Size of the effusion on chest radiograph (a grading of ≤2 vs >2 and/or having an intercostal catheter in place).^[31]^

The research team, treating physician, nursing staff, and participant will be blinded to the treatment arm. Only pharmacy staff will receive unblinded randomization information in order to prepare the study drug or placebo. In the event that unblinding is required, a designated member of the lead research team will be contacted and will follow the unblinding SOP.

### Data collection

2.6

Recruited participants will have their baseline data collected including chest radiograph appearances, blood tests (total leukocyte count, CRP) and clinical observations, as shown in Table 1. These parameters will be repeated through the participant's hospitalization and on discharge. Participants will be monitored for adverse events and those requiring interventional management will be noted. All participants will have a capillary blood glucose test four times a day. Participants will be asked to complete the SF-36 quality of life questionnaire at their date of recruitment, at time of hospital discharge and at the Day 30 follow-up visit. Additional blood tests and imaging will be performed at the discretion of the treating physicians. At the 6 and 12 months follow-up visits data on chest x-ray, spirometry, and adverse events will be collected.

Physical activity patterns will be evaluated by a well-validated triaxial accelerometer (ActiGraph GT3X+, Pensacola, FL). The accelerometer will be worn for a 7-day period post-discharge and also from day 30. Participants will fill an activity log while wearing the accelerometer. This objective measurement of physical function has been studied predominantly in people with malignant disease and is expected to be a useful adjunct in assessment of recovery from pneumonia in the future.^[32]^ Accelerometry will be performed on participants at the lead site only.

Where participants do not attend planned study visits the research staff will contact them at home to determine the reason and book an additional visit if required. If the participant misses a visit due to an admission to the site hospital, the visit will be carried out in the hospital providing the participant is well enough. Where this is not possible and the visit is missed, a File Note will be created and kept in the participant's study file. Study visits are carried out according to the individual participant's visit schedule.

### Data management

2.7

Data collected will be stored at site on password-protected computers accessible only by the site research staff and will be held in the department where the principal investigator (PI) is based.

Data entered will be checked by a second staff to ensure accuracy. All physical documentation will be stored in a secure environment in line with the Australian Code for the Responsible Conduct of Research for clinical trials and local policy guidelines for research data archiving.

### Statistical methods

2.8

Data will be analyzed on an intention-to-treat basis. Intergroup comparison will be conducted using Student *t* test or Mann–Whitney *U* rank sum test (for parametric and non-parametric distributions, respectively). Changes in parameters before and after treatment within the same subject will be analyzed using a paired *t* test or Wilcoxon signed rank test. Correlations will be analyzed using Pearson or Spearman tests. Multivariate analyses may be performed if indicated. *P* < .05 will be considered statistically significant in the data analyses.

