### Study design and participants

2.1

STOPPE is a multicenter, double-blinded, placebo-controlled RCT which will recruit participants with parapneumonic effusion. Participants will be randomized 2:1 to receive intravenous dexamethasone (4 mg twice daily for 48 hours) or placebo. This study will follow participants through their hospital admission and at outpatient visits after 14 days, 30 days, 6 months, and 12 months (Table 1).

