### Sample size

2.4

In the absence of existing data, this pilot study aims to recruit 80 participants over 18 months. This will allow inclusion of the full range of parapneumonic effusions at various stages from simple parapneumonic stage (most common) to empyema (about 5–10% of all cases). The 2:1 randomization strategy will include 50+ participants into the dexamethasone arm to increase the power of detecting treatment related adverse events. The results of this pilot study will inform the power calculation of future studies and determine the most appropriate endpoints of future trials. Past evidence and data suggest that we will be able to estimate a range of outcome parameters with a high enough degree of accuracy with a sample size of 80 and allow some initial comparisons between treatment and placebo. The number of patients included over this timeframe will inform the feasibility and design of further studies.

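### The equal-variance Student t test is named for a 2:1 trial of 80, where its standard error is wrong if the arms differ in spread; Welch's test is a cheap replacement

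*Protocol article*

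**What the plan says.** Section 2.8 (Statistical methods) of the protocol article states the between-arm method directly: "Intergroup comparison will be conducted using Student" t test or the Mann–Whitney U test, "for parametric and non-parametric distributions, respectively". It does not mention an unequal-variance form of the t test. The significance rule is P "< .05 will be considered statistically significant in the data analyses"; sidedness is not given.

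Allocation is unequal by design. Section 2.5 says "Participants will be randomly assigned (2:1) to receive intravenous dexamethasone or placebo", and section 2.1 says the same. Section 2.4 sets the size ("this pilot study aims to recruit 80 participants over 18 months") and the consequence for the larger arm: "The 2:1 randomization strategy will include 50+ participants into the dexamethasone arm". That section opens with "In the absence of existing data" and gives no SD, effect size or power. It also says that the results will feed the power calculation and endpoint choice of later studies.

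**The concern.** Student's t test estimates one common variance from both arms. When the arms are the same size, the pooled standard error equals the correct one even if the spreads differ. When one arm is about twice the other, the larger arm dominates the pooled variance. The standard error is then too small if the smaller arm is the more variable, and too large if it is the less variable.

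Unequal spread is plausible here. The hypothesis in the Introduction is that steroids act by reducing inflammation, and section 2.3 lists CRP and leukocyte count among the outcomes. For positive, right-skewed markers, a lower level often goes with a smaller spread. Placebo, the smaller arm, would then be the more variable one, which is the direction that makes intervals too narrow and P values too small.

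What is at stake is how far the trial's first comparisons can be trusted when endpoints are chosen for a later trial. The estimated mean difference and the SD of each arm do not depend on which t test is used; the standard error, P value and any interval do.

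**Working it through.** **Inputs.** Total 80 (section 2.4); allocation 2:1 (sections 2.1 and 2.5); threshold 0.05 (section 2.8), taken as two-sided. The ratio of the two SDs is an assumption, because the article gives none; it is shown from 0.5 to 2.

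**Arm sizes.** 80 × 2/3 = 53.3 and 80 × 1/3 = 26.7, so 53 v 27. This agrees with the article's figure of 50+ on dexamethasone.

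**Formulas.** With n₁ = 53 (dexamethasone) and n₂ = 27 (placebo):

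- Pooled variance = (52 s₁² + 26 s₂²)/78 = (2 s₁² + s₂²)/3.
- Student's squared standard error = pooled variance × (1/53 + 1/27) = pooled variance × 0.0559.
- True squared standard error = s₁²/53 + s₂²/27.

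**Worked case, placebo SD 1.5 times the dexamethasone SD (s₁ = 1, s₂ = 1.5).** Pooled variance = (2 + 2.25)/3 = 1.417. Student: 1.417 × 0.0559 = 0.0792. True: 1/53 + 2.25/27 = 0.1022. Ratio of standard errors = √(0.0792/0.1022) = 0.88, so Student's is 12% too small.

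**All cases.** The smaller SD is set to 1. The last column is the simulated error of Student's t for normal data with equal means.

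| More variable arm | SD ratio | Student SE² | True SE² | Student SE / true SE | Error at nominal 5% |
|---|---|---|---|---|---|
| Placebo | 2 | 0.1118 | 0.1670 | 0.82 | about 10.9% |
| Placebo | 1.5 | 0.0792 | 0.1022 | 0.88 | about 8.6% |
| Placebo | 1.25 | 0.0664 | 0.0767 | 0.93 | about 6.6% |
| Neither | 1 | 0.0559 | 0.0559 | 1.00 | about 5% |
| Dexamethasone | 1.25 | 0.0769 | 0.0665 | 1.07 | about 3.6% |
| Dexamethasone | 1.5 | 0.1025 | 0.0795 | 1.14 | about 2.7% |
| Dexamethasone | 2 | 0.1677 | 0.1125 | 1.22 | about 1.8% |

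Separate simulations with 40,000 and 200,000 trials per setting agree within simulation error (for example 8.4% to 8.6% at placebo SD 1.5 times). Welch's test stays at 4.8% to 5.2% in every row.

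**Is the allocation the cause?** At 40 v 40, Student's squared standard error is ((s₁² + s₂²)/2) × (2/40) = (s₁² + s₂²)/40, which is the true value whatever the SDs. Simulated error there is 5.0% to 5.1% over the same range. The fault comes from pairing the pooled test with unequal arms.

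**Skewed raw data.** For lognormal data with equal means and placebo SD 1.5 times, two simulations gave Welch 6.7% and 7.0%, against Student 8.0% and 8.4%. Welch is better, but not at its nominal level.

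**Cost of Welch.** With equal SDs and a difference of 0.65 SD at 53 v 27, simulated power was 76.6% for Welch and 77.2% for Student. A second run gave 76.8% v 77.3%.

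**The case against.** The strongest objection is that the error rates above describe an unlikely drug. If dexamethasone does nothing, randomization gives both arms the same distribution, the SDs are equal and Student's t is correct. If it does reduce inflammation, the mean CRP differs as well and a rejection is not a false positive. The 10.9% figure needs a drug that changes the spread and leaves the mean exactly where it was. This stands as a limit on reading the figures as a false-positive rate for the trial. It does not remove the point, because the standard error is wrong whether or not the means differ. For normal data, the non-coverage of a 95% interval built on the pooled standard error equals the error in the table. At placebo SD 1.5 times, such an interval would cover about 100 − 8.6 = 91.4%.

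Second, if dexamethasone lowers CRP by a constant proportion, the SDs on the log scale are equal and the problem disappears there. That is correct, and it supports choosing the log scale for such markers.

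Third, few endpoints are affected. Many in section 2.3 are proportions, survival or times to an event, and clearly skewed measures would go to Mann–Whitney under the plan as written. Actigraphy is done at the lead site only, and drained volume is recorded only if a catheter is inserted, so 53 v 27 does not describe either. This stands. The article also plans tests and mentions no confidence intervals, and calls itself an exploratory pilot, so the consequences are limited.

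A reader might also infer that the team will choose between the two tests after seeing unblinded results, and that this choice inflates error. The article does not say so. It links each test to a type of distribution and leaves open how and when that is judged. Assigning tests to endpoints is normal content for an analysis plan that is not shown here, so its absence from a condensed article is no fault.

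**Conclusion.** The concern holds in a conditional form. The article fixes an equal-variance t test and a 2:1 allocation, and the second removes the protection that the first would have had with equal arms. If the SDs differ by a factor of 1.25 to 2, Student's standard error is about 7% to 18% too small when placebo varies more, and about 7% to 22% too large when dexamethasone varies more. The standard-error figures follow from the formulas at 53 v 27; the error rates also assume normal data, equal means and a two-sided 5% test.

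It would go too far to say that the trial's P values will be wrong. No SDs are given, and with equal spread, or no drug effect of any kind, the planned test is valid. This is a minor to moderate point: an improvement to a stated method in a pilot, confined to continuous endpoints compared by t test.

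**What to change.** In section 2.8, replace Student's t test with Welch's unequal-variance t test for between-arm comparisons of means, and report the mean difference with its 95% confidence interval. For right-skewed markers such as CRP, make the comparison on the log scale and present it as a ratio of geometric means, because Welch's test is not fully calibrated on skewed raw data.

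The change is to wording only; no data collection, allocation or sample size is affected. It costs about half a percentage point of power when the SDs are equal. On the log scale the effect is read as a ratio instead of a difference in original units.

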### Outcomes

2.3

As a pilot and first study of corticosteroid in adults with pneumonia-related pleural effusions, we aim to capture a wide range of clinically relevant endpoints which have been used in clinical trials of pneumonia and/or pleural infection, and are considered by clinicians as important. These include:

1.The time to clinical stability defined as the time in hours for all of the following parameters to have been maintained for at least 12 hours: temperature ≤37.4°, heart rate ≤100 bpm, respiratory rate ≤20/min, oxygen saturations ≥95% on room air (unless on home oxygen), systolic blood pressure ≥90 mmHg and tolerating oral intake or discharge home (determined by the treating physician)^[28]^;2.The time in hours for each of the above parameters to have been maintained for least 12 hours;3.Change in leukocyte count and C-reactive protein (CRP) over time (Day 0, 1, 3, 14 ± 2 days, 30 ± 2 days);4.Proportion of participants with a normal leukocyte count and CRP at Day 14 ± 2 and Day 30 ± 2;5.Improvement in pleural effusion including size of pleural opacity as percentage of hemithorax (as used in our prior studies)^[29]^ over the first 14 ± 2 days and at Day 30 ± 2 compared with baseline; and proportion of participants whose effusion has resolved at day 14 ± 2 days and day 30 ± 2;6.Proportion of participants requiring an invasive pleural procedure including therapeutic aspirate (volume >200 mL) or chest drain insertion at <48 hours and >48 hours post-commencement of treatment. If intercostal catheter is inserted, the following will be recorded:a.Duration of chest tube drainage;b.Volume of fluid drained daily;c.Proportion treated with intrapleural fibrinolytic therapy; andd.Proportion requiring additional drainage procedures including additional chest drain insertion and therapeutic thoracentesis.7.Proportion of patients referred for thoracic surgery;8.Duration of antibiotic therapy (intravenous and oral);9.Length of hospital stay from commencement of treatment to discharge or death;10.Quality of life measurements including Short form-36 (SF-36) questionnaire^[30]^ and actigraphy (see Section 2.7 for details);11.Adverse events including but not limited to hyperglycemia, insulin use, need for intensive care, nosocomial infection, gastrointestinal bleeding and re-admission to hospital of any cause; and12.Overall survival.

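### The only test named for before/after changes is a within-subject paired test, which cannot isolate a dexamethasone effect, and the between-arm tests named are valid but not baseline-adjusted and so lose precision

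*Protocol article*

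**What the plan says.** Statistical methods (2.8) lists two separate kinds of test. For the arms: "Intergroup comparison will be conducted using Student" t or Mann–Whitney U, depending on distribution. For change: "Changes in parameters before and after treatment within the same subject will be analyzed using a paired" t or Wilcoxon signed rank test. Adjustment appears only as "Multivariate analyses may be performed if indicated", with no model, covariates or trigger. One threshold covers everything: P "< .05 will be considered statistically significant in the data analyses". Analysis is by intention to treat.

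Section 2.8 does not tie any test to any endpoint. Outcomes (2.3) words two items as change: "Change in leukocyte count and C-reactive protein (CRP) over time" on Days 0, 1, 3, 14 and 30 (item 3), and "Improvement in pleural effusion including size of pleural opacity as percentage of hemithorax" relative to baseline over the first 14 days and at Day 30 (item 5). SF-36 (item 10) is not worded as a change, but Data collection (2.6) has it completed at recruitment, discharge and Day 30. Section 2.6 also confirms baseline radiograph, leukocyte count and CRP. Effusion size, and a score that contains CRP, are minimization factors (2.5).

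**The concern.** The trial asks whether dexamethasone does better than placebo. A paired test within an arm asks whether patients changed. Patients treated for pneumonia can be expected to improve in either arm, so a significant paired test is compatible with no drug effect at all.

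The 2:1 allocation adds an asymmetry. With about twice as many patients on dexamethasone, the same recovery reaches P < .05 more often in that arm. Anyone who sets the two within-arm P values side by side will tend to see a benefit that is only a difference in sample size.

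The second issue is precision. The between-arm tests named use no covariate, although the baseline values are collected. In a trial of 80 that widens intervals for no return. Section 2.4 says the results will inform the power calculation and the choice of endpoints for later trials, so weak or misread contrasts would be carried forward.

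**Working it through.** **1. Arm sizes.** Sample size (2.4): "this pilot study aims to recruit 80 participants over 18 months", and "The 2:1 randomization strategy will include 50+ participants into the dexamethasone arm". 80 × 2/3 = 53.3, so about 53 v 27, which agrees with the stated 50+. The 80 is a pragmatic pilot number with no effect size or SD behind it, so there is no power figure to reproduce.

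**2. Paired tests when the drug does nothing.** Assumptions not in the documents: two-sided 0.05, and the same true mean change d in both arms, in units of the SD of the within-patient change. The power of a paired t test is the probability that a noncentral t with n − 1 degrees of freedom and noncentrality d√n exceeds the critical value in either direction. The arms are independent, so P(dexamethasone significant, placebo not) = p₅₃ × (1 − p₂₇), and the reverse is p₂₇ × (1 − p₅₃).

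| d | p₅₃ | p₂₇ | dexamethasone only | placebo only |
|---|---|---|---|---|
| 0.2 | 0.298 | 0.170 | 25% | 12% |
| 0.3 | 0.573 | 0.324 | 39% | 14% |
| 0.35 | 0.706 | 0.418 | 41% | 12% |
| 0.4 | 0.815 | 0.517 | 39% | 10% |
| 0.5 | 0.947 | 0.706 | 28% | 4% |
| 0.6 | 0.990 | 0.851 | 15% | 1% |
| 0.8 | 1.000 | 0.979 | 2% | 0% |
| 1.0 | 1.000 | 0.999 | 0.1% | 0% |

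For example, at d = 0.4: 0.815 × (1 − 0.517) = 0.394, and the reverse is 0.517 × (1 − 0.815) = 0.096. The rate peaks near d = 0.35. By d = 1.0 both arms are nearly always significant. The discordance has then gone, but the tests still say nothing about the drug.

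**3. Validity of the between-arm tests.** In a simulation with no drug effect, a shared recovery of 1.0 SD of the measure, 53 v 27 patients and 4,000 runs at each correlation, type I error was 0.040 to 0.055 across the t test on follow-up values, the t test on change scores and ANCOVA. All three are sound.

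**4. Precision of the between-arm tests.** Let r be the baseline–follow-up correlation (assumed 0.3, 0.5, 0.7) and take equal SDs at both times. Relative variances of the treatment contrast are 1 for the follow-up value, 2(1 − r) for the change score and 1 − r² for ANCOVA. Power is for an illustrative difference of 0.6 SD, 53 v 27, by noncentral t; the standard error is √(1/53 + 1/27) = 0.236 SD times the square root of the relative variance.

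| r | variance: follow-up / change / ANCOVA | power: follow-up / change / ANCOVA |
|---|---|---|
| 0.3 | 1 / 1.40 / 0.91 | 71% / 56% / 75% |
| 0.5 | 1 / 1.00 / 0.75 | 71% / 71% / 82% |
| 0.7 | 1 / 0.60 / 0.51 | 71% / 90% / 94% |

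At r = 0.5, adjustment makes 80 patients worth about 80/0.75 = 107 analysed without it. At r = 0.3 the saving against a change score is 1 − 0.91/1.40 = 35%. At r = 0.7 it is 1 − 0.51/0.60 = 15%.

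**The case against.** The case on the other side has real force.

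- *An intergroup comparison is planned, and is named first.* True. A reader might infer that the paired tests are the planned evidence of efficacy, or that the arms will be compared through their within-arm P values. The text says neither, and it does not rule out an intergroup test on the changes. The discordance rates above are therefore conditional on such a misreading.
- *The t test between arms is valid.* True. It is tempting to say that the unadjusted t test also mistakes recovery for drug effect. It does not: recovery is common to the randomized arms, and type I error stays near 5%. Its fault is lost precision.
- *Baseline is not necessarily discarded.* True. A paired test and a change score both use it. It goes unused only if follow-up values alone are compared, and 2.8 does not say which. What is missing from every named between-arm test is adjustment.
- *No test is assigned to CRP, leukocytes, effusion size or SF-36.* True. The link to the first three is inferred from 2.3, and SF-36 comes in only because it has a recruitment measurement.
- *The size depends on undocumented inputs.* True. Shared changes near 0.35 SD give the worst result and large ones almost none, so only the range can be reported. The gain from ANCOVA over change scores is likewise small if r is high.
- *This is an exploratory pilot reported in a condensed article, and a separate analysis plan may give the model.* This lowers the severity. It does not remove the point, because the paired test is a choice that the article states and attaches to a significance threshold.

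**Conclusion.** The point holds in a limited form. The one method fixed for before/after change cannot answer the trial's question, and the between-arm tests named are valid but less precise than the data allow. If within-arm P values were compared across the arms with no drug effect, the misleading pattern favouring dexamethasone would arise in anything from almost no trials to about 41%, depending on an assumed shared change of 0.2 to 1.0 SD. The precision forgone against ANCOVA, in variance, is 9%, 25% or 49% for follow-up values and 35%, 25% or 15% for change scores, at assumed correlations of 0.3, 0.5 and 0.7. These figures rest on equal SDs at the two times and normal data.

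The documents do not support saying that the planned analysis as a whole confuses recovery with drug effect. For an exploratory pilot this should be changed, but it does not undermine the trial.

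**What to change.** Replace the paired-test sentence in 2.8. For leukocyte count, CRP (log scale), percent hemithorax and SF-36, compare the arms by ANCOVA at each scheduled time, or by a repeated-measures mixed model over the scheduled times, with the baseline value as covariate and preferably the minimization factors from 2.5. Report the adjusted difference with its 95% confidence interval at each time, as a ratio for CRP. Present within-arm changes descriptively, without P values.

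The cost is a few lines of statistical wording. The baseline values are already collected, and neither sample size nor visit schedule changes.

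### Allocation is minimized on three factors but the stated between-arm tests leave them out, so to the extent the factors predict outcome the tests are conservative and some precision is forgone

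*Protocol article*

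**What the plan says.** Protocol article, section 2.5 (Randomization and blinding): "Participants will be randomly assigned (2:1) to receive intravenous dexamethasone or placebo". The same section states "Randomization is minimized for" and lists three two-level factors:

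- a predictive score, below 2 versus 2 or more, described as a score "for the development of complicated pleural effusion/empyema secondary to pneumonia";
- known diabetes, yes versus no;
- radiographic effusion grade, 2 or less versus more than 2 and/or an intercostal catheter already in place.

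Section 2.8 (Statistical methods): "Intergroup comparison will be conducted using Student" t test or the Mann–Whitney U test, with significance at P < .05. Neither test uses covariates. The one sentence that touches on adjustment is "Multivariate analyses may be performed if indicated". It names no covariates, gives no trigger and does not refer to the minimization factors.

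Section 2.4 (Sample size): "In the absence of existing data, this pilot study aims to recruit 80 participants over 18 months". No effect size, SD or power is given. The section expects the results to support initial between-arm comparisons and the power calculations of later trials.

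**The concern.** Minimization forces the arms to be alike on the three factors. Whatever part of the outcome the factors explain is thereby largely removed from the difference between arm means. A two-sample t test does not know this. Its standard error is built from the total within-arm variance, which still contains the between-factor variation. The reported standard error is then larger than the real sampling variability of the estimate, the interval is too wide, and the test rejects less often than its nominal level. The rank test behaves in the same way.

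At stake is precision in a small trial with about 27 placebo patients, and the quality of the estimates handed on to later studies. A secondary point is that a conditional sentence without a trigger leaves the choice between adjusted and unadjusted results open until the data have been seen.

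**Working it through.** **Inputs from the document.** N = 80; allocation 2:1; three binary minimization factors; unadjusted t or Mann–Whitney test; alpha 0.05 (sidedness is not stated; two-sided is assumed). There is no power figure to reproduce. The one arithmetic check available is 80 × 2/3 = 53.3 and 80 × 1/3 = 26.7, which agrees with the stated aim of 50+ on dexamethasone.

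**Assumptions not in the document.** R², the share of outcome variance explained by the three factors, is varied from 0 to 0.3. The simulation also assumes factor prevalences of 0.50, 0.25 and 0.40, equal contributions of the factors, a normal outcome, and a biased-coin minimization.

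**Step 1: reference effect.** In total-SD units the unadjusted standard error is √(1/53.3 + 1/26.7) = 0.237. The effect detectable with 80% power is (1.960 + 0.842) × 0.237 = 0.66 SD. The calculations below use 0.666 SD (about 0.67).

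**Step 2: approximation under perfect balance.** The true SD of the estimate is 0.237 × √(1 − R²), so the standard error is inflated by 1/√(1 − R²).

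- True size = 2 × [1 − Φ(1.96/√(1 − R²))].
- Unadjusted power = Φ[(0.666 − 1.96 × 0.2372)/true SD].
- Adjusted power = Φ[0.666/true SD − 1.96].

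| R² | Inflation | True SD | True size | Power, unadjusted | Power, adjusted | Gap (points) |
|---|---|---|---|---|---|---|
| 0 | 1.00 | 0.237 | 5.0% | 80% | 80% | 0 |
| 0.1 | 1.05 | 0.225 | 3.9% | 81% | 84% | 3 |
| 0.2 | 1.12 | 0.212 | 2.8% | 83% | 88% | 5 |
| 0.3 | 1.20 | 0.198 | 1.9% | 84% | 92% | 7 |

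**Step 3: simulation with imperfect balance** (6,000 null and 3,000 alternative trials per row; adjusted = linear model with the three factors as main effects).

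| R² | t-test SE / true SD | Size: t | Size: Mann–Whitney | Size: adjusted | Power: t | Power: adjusted |
|---|---|---|---|---|---|---|
| 0 | 0.236 / 0.235 | 4.9% | 4.8% | 4.8% | 80% | 80% |
| 0.1 | 0.237 / 0.227 | 4.4% | 4.3% | 5.7% | 80% | 83% |
| 0.2 | 0.237 / 0.215 | 3.0% | 2.9% | 4.9% | 82% | 87% |
| 0.3 | 0.237 / 0.203 | 2.2% | 2.3% | 5.3% | 83% | 91% |

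The t-test standard error is about 4%, 10% and 17% too wide at R² = 0.1, 0.2 and 0.3. The Monte Carlo standard error is about 0.3 points for size (√(0.05 × 0.95/6000)) and 0.7 points for power (√(0.8 × 0.2/3000)). A separate simulation with the same N and ratio gave t-test sizes of 5.2%, 3.9%, 3.1% and 2.1% for R² = 0, 0.1, 0.2 and 0.3.

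**Step 4: attribution.** With simple randomization in place of minimization, the same t test had a size of 5.0% to 5.1% at R² = 0 to 0.3. The conservatism therefore comes from minimizing and then leaving the factors out.

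**The case against.** The strongest reply is that this is a condensed article. The full protocol and any analysis plan are not shown, covariate lists usually live there, and the conditional sentence does not rule adjustment out. That would settle the matter if section 2.8 were silent, but it names the between-arm tests, and those tests do not match section 2.5. An unseen plan may already put this right; the text at hand does not.

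Four other parts of the reply stand, and they limit the point.

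- **The loss is conditional.** A reader might infer that the intervals are certainly too wide. The document gives no figure for how predictive the factors are. At R² = 0 nothing is lost, and at 0.1 the effect is slight. Only the score is described as predictive, and of complicated effusion or empyema; the reasons for including diabetes and effusion size are not given.
- **Power does not collapse.** If the effect is fixed at 0.67 of the residual SD, simulated unadjusted power falls to 73% at R² = 0.2 (80% adjusted) and 65% at 0.3 (78% adjusted). That drop arises largely because total SD grows with R² on that scale. At a fixed total-SD effect, unadjusted power does not fall; the planned test simply forgoes a gain.
- **No false positives follow from the unadjusted tests.** The error is conservative. A reader might also infer from the conditional sentence an intention to report the more favourable result. The text leaves that choice open but shows no such intention, and none of the calculations address it.
- **Adjustment of every comparison is not workable.** Three binary factors make eight cells. With the assumed prevalences the rarest cells expect 80 × 0.50 × 0.25 × 0.40 = 4 patients, about 1.3 on placebo. Fully stratified tests, or adjusted models for rare events such as death or surgical referral, could be unstable.

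**Conclusion.** The mismatch between sections 2.5 and 2.8 is real, and its direction is clear: where the minimization factors predict the outcome, the stated tests are conservative and their standard errors too wide. The size is modest. For an assumed R² of 0.1 to 0.3, true size is about 4% down to 2%, and adjustment would gain about 3 to 8 points of power at an effect of 0.67 total SD. Adjustment keeps size near 5% and costs nothing appreciable if the factors prove uninformative.

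The figures rest on assumed R², prevalences, coin probabilities and a normal outcome. Proportions and time-to-event models were not simulated, so the numbers should not be carried over to them. Because the trial is an exploratory pilot without a power calculation, severity is low to moderate. The main consequence is for the stated aim of informing later power calculations, since the precision available from this design would be understated.

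**What to change.** In section 2.8, replace the conditional sentence on multivariate analysis with a fixed rule:

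- **Continuous and time-to-event outcomes:** the main between-arm comparison is a linear or mixed model, or a Cox model, with the three minimization factors as main effects, coded as used at randomization.
- **Proportions:** an adjusted or standardized risk difference where the number of events allows.
- **Sparse outcomes, such as death or surgical referral:** an unadjusted comparison, named in advance as the fallback.
- **Student t and Mann–Whitney tests:** kept as supportive analyses.

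Main effects rather than full cross-classification avoid the problem of near-empty cells. The cost is one paragraph of wording. The factors must already be known to randomize each participant, so no extra data collection is needed. If a separate analysis plan already specifies this adjustment, it is enough to align section 2.8 with it.
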